## Abstract

**Background:** After a coma, patients with severe brain injury may present disorders of consciousness (DOC). A substantial proportion of these patients also suffer from severe dysphagia. Assessment of and therapy for swallowing disabilities of patients with DOC are essential because dysphagia has major functional consequences and comorbidities. Dysphagia evaluation in patients with DOC is impeded by the lack of adapted tools. The first aim of this study was to create a new tool, the SWallowing Assessment in Disorders Of Consciousness (SWADOC), and propose a validation protocol. The SWADOC was developed to help therapists assess factors related to swallowing in patients with DOC. The second aim was to investigate the relationship between patients' level of consciousness and SWADOC items and scores.

**Method/Design:** In this multicenter prospective cohort, 104 patients with DOC will be tested three times over five consecutive days with the SWADOC. Statistical analyses will focus on the reliability and validity of the SWADOC, especially the intrarater and interrater reliability, internal consistency, measures of dispersion, and concurrent validity with the Facial Oral Tract Therapy Swallowing Assessment of Saliva (FOTT-SAS). The level of consciousness will be assessed with the Simplified Evaluation of CONsciousness Disorders (SECONDs) and the Coma Recovery Scale-Revised (CRS-R).

**Discussion:** The assessment of swallowing abilities among patients with DOC is the first necessary step toward the development of a customized dysphagia care plan. A validated scoring tool will be essential for clinicians to better assess dysphagia in patients with DOC and document the evolution of their disorders.

**Trial Registration:** NCT04706689.

## Introduction

After a coma, some patients with severe brain injury will develop an altered state of consciousness before recovering partial or complete consciousness. Disorders of consciousness (DOC) consist of three states ranging from no awareness and no arousal to the preservation of arousal with fluctuating awareness (1): coma (2), vegetative state/unresponsive wakefulness syndrome (UWS) (3, 4), and minimally conscious state (MCS) (5). Patients with UWS typically exhibit only oromotor reflexes, blinks, and startle responses, as well as withdrawal from noxious stimuli (3). These patients do not respond to command and do not show visual pursuit or fixation. Individuals with MCS show reproducible but inconsistent signs of consciousness, such as following commands, visual pursuit or fixation, and localization of noxious stimuli (5). MCS has been subcategorized into MCS PLUS (MCS+) and MINUS (MCS–) based on the complexity of the observed responses: MCS+ describes high-level behavioral responses (i.e., following commands, intelligible verbalizations, intentional communication using a gestural or verbal yes/no code), and MCS– describes low-level behavioral responses (i.e., automatic motor behaviors, object manipulation, localizing objects in space, localizing noxious stimuli, visual pursuit or fixation) (6, 7). When patients recover the ability to functionally communicate or to use objects appropriately, we consider that they have emerged from MCS (EMCS) (5). The currently recommended scale for the behavioral assessment of consciousness is the Coma Recovery Scale–Revised (CRS-R) (8), as it fulfills all the Aspen Neurobehavioral Workgroup criteria (9). The CRS-R has an oromotor subscale that includes the assessment of basic oromotor reflexes and vocalizations or verbalizations, but no swallowing components are integrated in this scale. Recently, the Simplified Evaluation of CONsciousness Disorders (SECONDs) scale (10, 11) was developed based on the most prevalent signs of consciousness observed using the CRS-R (12). This tool is quick and easy to administer (11).

Almost all patients with DOC have severe dysphagia (13), requiring the use of ventilation and nutritional support (i.e., tracheostomy, gastrostomy) to limit the occurrence of comorbidities (e.g., bronchopulmonary infection, undernutrition). Individuals with DOC classically receive hydration and nutrition through an enteral feeding tube (14), and a large majority will not be able to return to exclusively oral feeding (13, 15). An objective swallowing assessment using fiber-optic endoscopic or videofluoroscopic swallowing evaluations is required in patients with DOC, for whom the possibility of partial or total oral feeding is being considered. These examinations, performed by experienced clinicians, constitute the gold standard tool for assessing dysphagia in this population. Indeed, these examinations allow clinicians to precisely analyze the mechanisms at play during swallowing and to detect possible silent aspirations, which are very prevalent in patients with DOC (13). As Mélotte et al. (13) showed in a cohort of 92 patients, the risk of silent aspiration is high for these patients, as 48% of DOC patients do not have a cough reflex. Moreover, 28% presented saliva aspiration, 13% aspiration with thick texture, and 32% aspiration with liquid texture. A lack of knowledge of the specific features of DOC prevents some clinicians from performing these exams. Moreover, performing a functional swallowing test (liquid and food test) can be difficult in patients with severe trismus (lockjaw) or total absence of the oral phase of swallowing, but as long as a partial oral phase with initiation of swallowing exists, thick or liquid swallowing can be tested (13, 16–18).

In daily practice, speech therapists help document the presence or absence of a range of components required for swallowing in order to guide therapy and monitor its effectiveness by repeated assessment over time. The clinical reality of patients with DOC, mainly the lack of response to simple motor commands (in UWS and MCS–) and functional communication, makes it difficult to fully understand and appropriately treat their swallowing disorders. For these reasons, classical swallowing assessment at the bedside can be unsuitable for this population. There is a lack of appropriate bedside tools to appraise and monitor swallowing disorders in patients with DOC. The impossibility of orienting interventions based on determined quantitative and qualitative swallowing components makes it more difficult to develop a treatment plan and assess the patient's progress.

Our recent DOC cohort study (13) found some links between swallowing and the level of consciousness. In particular, none of the patients with UWS and only a minority of the patients in MCS exhibited an effective oral phase of swallowing (adequate lip prehension, tongue propulsion, and no post-swallowing oral stasis). However, these links are not yet completely understood, and further studies are necessary to increase our knowledge of which components of swallowing are linked to consciousness and to what extent. In this context, the validation of a tool that focuses on qualitative and quantitative swallowing components will help us identify swallowing behaviors that may be considered unequivocal signs of consciousness in patients with DOC. These results may eventually contribute to the development of new diagnostic guidelines for DOC that would include swallowing behaviors in their criteria.

The aim of this article is to present a protocol that develops and validates the SWallowing Assessment in Disorders Of Consciousness (SWADOC). This tool will be administered repeatedly to a population of patients with DOC by different examiners, and intrinsic test characteristics will be calculated. The relationship between patients' level of consciousness and SWADOC scores will also be studied.

## Methods And Analysis

### Development of the Swallowing Assessment in Disorders of Consciousness

#### Identification of Domain(s) and Item Generation

The SWADOC was developed to overcome the lack of a suitable tool that would allow clinicians to assess and measure swallowing-related components in patients with DOC. It explores some of the oral and pharyngeal components of swallowing as well as a range of prerequisites and related components of swallowing. Our first aim was to develop a rapid, reliable quantitative tool. However, although quantitative items present advantages, many qualitative elements are also meaningful in fully understanding a patient's profile. Thus, we decided to include both quantitative and qualitative items.

This tool was developed by three speech therapists and then submitted for evaluation to 10 experts (otorhinolaryngologists and speech therapists) who work with patients with DOC. Their comments contributed to the final version. The development period lasted ~10 months.

The tool was developed based on both deductive and inductive methods (19). First, we examined literature in the field of consciousness and swallowing, and looked for existing scales (deductive method). The construction of the tool was inspired by actual knowledge on dysphagia in DOC patients based on the few studies dedicated to swallowing in DOC patients (13, 15, 18, 20).

The SWADOC was built based upon several existing tools: the Facial Oral Tract Therapy (FOTT) (21, 22), the SECONDs (10, 11), the New Zealand Secretions Scale (NZSS) (23), the Oral/Facial Sensitivity subtest of the Comprehensive Assessment Measure for Minimally Responsive Individuals (CAMMRI) (24), the stimulation method for sensory processing disorder (sensory dysorality) proposed by Senez (25), and the arousal protocol of the CRS-R (8). It includes some medical history information from the Food Intake LEVEL Scale (FILS) (26) and the International Dysphagia Diet Standardization Initiative (IDDSI) (27).

The SWADOC was inspired by the FOTT (22), as adapted for patients with DOC in French by Bicego et al. (21), and modified based on our day-to-day clinical experience with patients with DOC. The items assessing command following are based on the SECONDs principles (10, 11), insofar as response to verbal command is considered intact if the patient passes a minimum of two out of three trials. The item on quantitative saliva secretions is based on the NZSS (21), which assesses secretion severity during endoscopy by location, amount (as a percentage), and response. We used the percentages proposed in that scale and adapted them to the oral cavity. Since the oral area is larger than the laryngeal area, the percentages are more difficult to evaluate, but to our knowledge, there is no validated scale for the evaluation of accumulated secretions in the mouth. Tactile stimulation is inspired by Senez's stimulation method for sensory processing disorder (25). Finally, the SWADOC requires the examiner to perform an arousal protocol similar to the CRS-R (8) if the patient falls asleep during the procedure. The medical history taking subsection also features the IDDSI (27) score and the FILS (26) score.

We then applied the tool in routine clinical practice with patients with different levels of consciousness and adjusted some items as a result (inductive method).

#### Content Validity

Ten experts were asked to judge the SWADOC overall and per item with a Likert scale to solicit their opinion of its relevance in their clinical practice, its suitability for patients with DOC, and the clarity of the administration guidelines. The experts' responses focused on the clarity of certain instructions and suggested that some qualitative items be added and some quantitative items modified (levels that were too subjective or dependent on hospital functioning and not on patients themselves). These suggestions were analyzed and taken into account to improve the SWADOC by clarifying instructions, adding qualitative items, and modifying quantitative items.

### Presentation of the Tool

The tool is composed of 56 items: 48 qualitative items and a subsection called the “SWADOC-scored” comprising eight quantitative items. The instruction guide comprises (1) one page with general recommendations; (2) a list of required materials; (3) explanations of the quantitative items; (4) a detailed medical history; (5) the SWADOC-scored grid; and (6) a checklist and seven pages of instructions covering all the quantitative and qualitative items (Figure 1; Supplementary Materials 1, 2). The tool was translated into English for the convenience of readers of this paper. However, if an English validation is carried out, a back-translation method will be applied.

**Figure 1 F1:**
[figure not shown]
Description of the SWADOC. ENT, Ear, Nose, and Throat; SWADOC, SWallowing Assessment in Disorders Of Consciousness.

The “SWADOC-scored” subsection includes eight quantitative items (Figure 2; Supplementary Material 3). Four items are linked to the oral phase and four to the pharyngeal phase. For each quantitative item, patient's abilities are rated on a four-level scale ranging from 0 to 3. These levels correspond to item scores that can be added together to calculate three performance scores: the oral phase subscore (sum of the four oral item scores), the pharyngeal phase subscore (sum of the four pharyngeal item scores), and the total swallowing score (sum of the eight item scores).

**Figure 2 F2:**
[figure not shown]
SWADOC-scored (English version). DOC, disorders of consciousness; SWADOC, SWallowing Assessment in Disorders Of Consciousness.

The administration procedure for the test and the sequencing of items were designed to put patients in optimal conditions for the exam. For example, the therapist first introduces himself/herself, describes the assessment procedure, and then begins with external facial stimulation before doing the mouth cavity stimulation. The therapist assesses the patient at the bedside or in his or her usual chair and only if the patient is awake and shows no signs of pain or medical problem (e.g., fever, hypoxemia, and arrhythmia). In addition, during the assessment, some parameters for stopping are provided to avoid presenting stimulations that are inappropriate for the patient's abilities (e.g., swallowing a minimal amount of thickened liquid). All these recommendations are described in the administration guide.

The objectives of the SWADOC are to address all of the goals of an assessment tool: (1) document the prerequisites for swallowing; (2) determine the active ingredients of the therapy; (3) track changes in a patient's swallowing abilities; and (4) monitor the effectiveness of a therapy. In a scientific research context, the SWADOC will help us better understand the links between the level of consciousness and swallowing components.

### Study Design

This project is a multicenter prospective cohort study that will take place in several hospitals and clinics in Belgium and France. The SWADOC was created in French.

### Population and Recruitment

This study will be carried out in patients with DOC or emerging from DOC following severe acquired brain injury. Patients will be divided into four groups according to their clinical diagnosis, as assessed with the SECONDs and with the CRS-R: UWS, MCS–, MCS+, and EMCS. Participants will be recruited from inpatient neurological rehabilitation programs in post-coma units and rehabilitation services or among patients hospitalized for a multimodal assessment of consciousness for diagnostic and prognostic purposes.

Only patients who meet all of the following inclusion criteria will be considered for enrollment: (1) age above 18 years; (2) perfect knowledge of French language before the injury; (3) previous coma phase caused by a severe acquired brain injury; (4) medical stability (no mechanical ventilation or sedation, no acute medical pathology such as infection or respiratory distress); (5) no neurological or otorhinolaryngological disease that can impact swallowing prior to the brain injury; (6) minimum of 28 days since the acquired brain injury at inclusion (28, 29); (7) diagnosis of UWS, MCS–, MCS+, or EMCS based on the SECONDs and the CRS-R; (8) informed consent from the patient's legal representative; and (9) affiliated patient or beneficiary of a health insurance plan (for participants in France only).

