#### Power of the Study

The sample size was calculated using a power calculation (G * Power, Universities of Kiel, Mannheim, and Düsseldorf) in a one-way analysis of variance (ANOVA) with a significance level of 0.05 and a power of 0.8. Effect size is based on previous published data on swallowing performance in patients with DOC (13). Cohen's *d* was used to estimate the effect size; the result was 0.659, corresponding to an eta-squared of 0.0979. We round up and base our calculation on an effect size of 0.1, corresponding to an intermediate effect. In this context, a total sample size of 104 participants (26 per group) is needed to demonstrate a difference in SWADOC‘ subscores and total score between the four consciousness groups. If, by the end of June 2025 the sample size is not reached, we will discuss extending the data collection period if necessary.

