#### Reliability

The intrarater (i.e., SWADOC-scored vs. SWADOC-scored by the same examiner on the same day and on two different days) and interrater reliability (i.e., SWADOC-scored vs. SWADOC-scored on the same day by two different examiners) will be calculated in two separate analyses using weighted Fleiss's kappa coefficients (K_W_). A value below 0 will be considered to indicate poor agreement, between 0 and 0.2 slight agreement, between 0.21 and 0.4 fair agreement, between 0.41 and 0.6 moderate agreement, between 0.61 and 0.8 substantial agreement, and between 0.81 and 1 almost perfect to perfect agreement (32). We will also determine the internal consistency of the SWADOC-scored with Cronbach and Spearman intercorrelations to determine the interrelatedness of the constituent items.

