## Discussion

It is challenging to assess swallowing in patients with DOC because of the clinical reality of this population. This protocol describes a clinical study that will seek to validate the SWADOC, a tool adapted for bedside swallowing assessments in patients with DOC. The link between patients' level of consciousness and SWADOC scores will also be studied. To achieve these goals, a multicenter prospective cohort study design will be adopted.

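### By the protocol's own definition only 78 of the planned 104 patients have DOC, and no DOC-only reliability or validity estimate is specified for a tool to be validated in DOC

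*Protocol article*

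**What the plan says.** **Definition.** The Introduction states: "Disorders of consciousness (DOC) consist of three states ranging from no awareness and no arousal to the preservation of arousal with fluctuating awareness", and lists coma, UWS and MCS. It then sets EMCS apart: "When patients recover the ability to functionally communicate or to use objects appropriately, we consider that they have emerged from MCS (EMCS").

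**Target population.** The Discussion calls the SWADOC "a tool adapted for bedside swallowing assessments in patients with DOC".

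**Sample.** The Abstract says "104 patients with DOC will be tested three times over five consecutive days with the SWADOC". Population and Recruitment is wider: "This study will be carried out in patients with DOC or emerging from DOC following severe acquired brain injury", with UWS, MCS–, MCS+ and EMCS as the four groups. Power of the Study says "a total sample size of 104 participants (26 per group) is needed", the requirement for the four-group ANOVA.

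**Validation analyses.** Under Reliability, intrarater and interrater agreement "will be calculated in two separate analyses using weighted Fleiss's kappa coefficients", and internal consistency is added. Concurrent Validity plans the correlation with the FOTT-SAS, and Measures of Dispersion the floor and ceiling checks. None of these sections names a DOC-only or by-group result. Descriptive Analysis and the section relating swallowing components to levels of consciousness do specify analysis by group.

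**The concern.** There are two linked problems.

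The first is a contradiction of fact. The Abstract counts all 104 patients as having DOC, while the definition, the eligibility criteria and the group sizes together put a quarter of them outside it.

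The second is one of inference. Weighted kappa, alpha and correlations depend on the spread of true scores as well as on measurement error. A group that scores higher adds spread, so the pooled coefficient can be higher than in DOC patients even though no DOC patient is rated more accurately. The Introduction says bedside assessment is difficult in DOC because patients do not follow commands or communicate functionally. EMCS patients may have regained functional communication.

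Decisions depend on these results. Validation of the Study Procedure, Measures of Dispersion and Limitations and Pitfalls all make possible changes to items, instructions or the scale depend on agreement or on floor and ceiling findings. A favourable pooled figure could leave unchanged an item that works less well in the patients the tool is meant for.

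**Working it through.** **1. The plan's own figure.** Power of the Study gives d = 0.659. Then eta² = 0.659² / (0.659² + 4) = 0.4343 / 4.4343 = 0.0979, as stated. With eta² = 0.1, f = √(0.1/0.9) = 0.333. For four groups, N = 104 and alpha 0.05, the noncentral F gives power of 80.8%, so 104 (26 per group) reproduces.

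**2. The count.** EMCS: 26/104 = 25%. DOC: 3 × 26 = 78.

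**3. Effect of pooling on a coefficient.** Assume within-group variance 1, the same within-group coefficient r in every group, and between-group variance B. Then the coefficient is (r + B)/(1 + B). If only EMCS differs, by d within-group SD, B = 0.25 × 0.75 × d² = 0.1875d², and the rise over DOC-only is eta² × (1 − r), with eta² = B/(1 + B). For a fixed eta² this is the largest rise the model allows, because the DOC groups then contribute no spread of their own. A FOTT-SAS correlation follows the same formula if the shift is equal on both scales.

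At eta² = 0.1, B = 0.1/0.9 = 0.111 and d = √(0.111/0.1875) = 0.77:
- r = 0.60: 0.711/1.111 = 0.64, a rise of 0.04.
- r = 0.50: 0.611/1.111 = 0.55, a rise of 0.05.
- r = 0.80: 0.911/1.111 = 0.82, a rise of 0.02.
- Equally spaced group means: rise 0.018 (r = 0.60) or 0.009 (r = 0.80).
- Only UWS differs: change −0.007 or −0.003.

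Larger assumed shifts, r = 0.60:

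| d | Implied eta² | Pooled |
|---|---|---|
| 1 | 0.16 | 0.66 |
| 1.5 | 0.30 | 0.72 |
| 2 | 0.43 | 0.77 |

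**4. Simulated 0–3 items.** Each scenario has 200,000 patients, eight items and cut points −1, 0, 1. SDs are 0.8 (patient), 0.6 (item) and 0.5 (rating); the external score has error SD 0.9. Group means are assumed, in the order UWS, MCS–, MCS+, EMCS. Entries are pooled against DOC-only.

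| Assumed means | Quadratic kappa | Alpha | r |
|---|---|---|---|
| −0.45, −0.15, 0.15, 0.45 (small separation) | 0.745 / 0.737 | 0.886 / 0.879 | 0.635 / 0.621 |
| −1, −0.3, 0.3, 0.3 (EMCS equals MCS+) | 0.766 / 0.765 | 0.904 / 0.904 | 0.677 / 0.675 |
| −2, 0, 0.3, 0.6 (UWS near floor) | 0.821 / 0.821 | 0.937 / 0.937 | 0.766 / 0.767 |
| −1.5, −0.5, 0.5, 1.5 (large separation) | 0.849 / 0.805 | 0.951 / 0.928 | 0.803 / 0.738 |
| −1, −0.5, 0, 4 (EMCS near ceiling) | 0.867 / 0.746 | 0.958 / 0.890 | 0.838 / 0.644 |

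The last row gives +0.12 for kappa (0.867 − 0.746) and +0.19 for r (0.838 − 0.644).

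**5. Floor effects, from the protocol's own hypothesis.** Study Hypotheses expects UWS patients at level 0 on oral items 1, 3 and 4. If so, UWS alone puts at least 26/78 = 33% of DOC patients at floor on those items, but only guarantees 26/104 = 25% in the pooled sample. Dilution follows whenever EMCS patients are at floor less often than DOC patients.

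**6. Precision of a DOC-only result.** √(104/78) = 1.15.

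**The case against.** The strongest reply is that inflation is not shown. A reader might infer that the pooled coefficients will overstate performance in DOC. The documents do not support that: they give no EMCS score distribution, and the only effect size they contain is eta² of about 0.1, where the rise is small and can be slightly negative. The one group-specific score hypothesis concerns UWS at floor, and UWS stays in the DOC set. This part of the reply stands.

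A reader might also infer that a moderate kappa would be relabelled substantial. In a simulated item with cut points −0.2, 0.8, 1.6 and EMCS shifted by 1, 1.5 or 2 SD, quadratic kappa goes from 0.56 in DOC to 0.63, 0.69 or 0.75 pooled. Linear kappa goes from 0.42 to 0.48, 0.54 or 0.59 and stays moderate throughout. The protocol does not name the weights, so a change of band depends on the weights, the starting value and the assumed shift.

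Nor is there a quota: 26 per group is a sample-size target, with no enrolment cap stated.

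Recruiting EMCS is open and defensible. It serves the second aim, and a scale meant to track recovery needs data at emergence. That is a reason to keep the pooled estimate, though not for letting it stand alone for DOC.

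Finally, an analysis plan not shown here may hold subgroup estimates, and the planned group comparison of every item would reveal score differences. The first limits how firmly the missing DOC-only result can be called an error. The second shows mean differences, not agreement or validity within DOC. Neither removes the contradiction in the Abstract.

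**Conclusion.** The point holds in a limited form. Two things are certain from the text: the Abstract's count conflicts with the Introduction, the eligibility section and the group sizes, and the validation sections as written specify no result for the 78 planned patients who fit the stated target population.

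That pooling can flatter the tool is a real mechanism of unknown size. On the models above, the rise is about 0.05 or less at the planning eta² of 0.1 (for a within-DOC coefficient of 0.50 or more). It is nil if EMCS resembles MCS+, and about 0.04 for kappa and 0.07 for r under large, evenly spaced separation. Only if EMCS is assumed near the ceiling does it reach about 0.12 for kappa and 0.19 for r. The planning eta² is not a bound on the truth, and every score distribution here is an assumption. Dilution of floor effects needs less: it is enough that EMCS patients are at floor less often than DOC patients.

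The change is worth making because only a DOC-only estimate can show whether pooling mattered.

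**What to change.** - **Reliability, Concurrent Validity and Measures of Dispersion:** report each kappa, internal-consistency, FOTT-SAS and floor or ceiling result for UWS + MCS– + MCS+ (planned n = 78) alongside the pooled 104. State that conclusions about performance in DOC, including decisions to modify items, rest on the DOC-only result.
- **Relationship between swallowing components and levels of consciousness:** no change. The ANOVA keeps all four groups and 104 patients.
- **Abstract:** describe the 104 as patients with DOC or EMCS, 78 and 26 planned respectively.

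**Cost.** No extra patients or assessments. Confidence intervals for the DOC-only coefficients are about 15% wider, and those coefficients may be less favourable than the pooled ones.
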